#### *Secondary analyses—antenatal corticosteroid use*

Although the primary study outcome is neonatal mortality, a key secondary outcome is rate of antenatal corticosteroid use. The analytic approach for this outcome will be comparable with that described for the primary outcome in that both permutation and model-based analyses will be implemented.

The primary results likely will need to be substantiated with a sensitivity analysis of the results to missing outcome data. The need for a detailed sensitivity analysis will depend on the amount of missing data and any intervention-dependent pattern to the missing data. A first step will be to look for patterns by comparing observed characteristics of participants who have missing data with those having complete data. Then, if appropriate, both nonparametric and parametric approaches will be undertaken to evaluate the impact of missing data. Additional details will be provided in the Statistical Analysis Plan.

#### *Other secondary outcome measures*

The trial will also examine a number of additional clinical and process measures as secondary outcomes. For each of these outcome measures, descriptive statistics will be computed as described in the introductory paragraphs above. Model-based analyses will then be used to examine the effects of the intervention on each of clinical and process measures. For the clinical measures, GEE models will be used to evaluate the effect of the intervention on marginal risk of the outcome, with results reported for both unadjusted analyses and analyses controlling for covariates that differ across clusters. Also, generalized linear mixed models will be used to examine the effect of the intervention on subject-level risks. Again, results will be reported for both unadjusted and adjusted models.

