### Outcome measures

The primary outcome measure is neonatal mortality at 28 days of life in preterm infants in all clusters. LBW will be used as a proxy for preterm birth because in GN sites approximately 15% of the women who delivered at health centers or homes did not know their LMP dates, and 40% of the deliveries occurred at the community level, where ultrasound is not available. Thus, pragmatically, it is not possible to use gestational age to classify preterm births in these settings.

The variable to be used for classifying preterm births needs to be objective and unbiased in both intervention and control clusters. Thus it should be unrelated to the experimental intervention. The color-coded tape (Figure
4) is part of the intervention and will be used to improve the identification of pregnancies at high risk of preterm birth, but only in the intervention group. Therefore it is expected that this group will show more reliable gestational age assessment during the intervention period. Consequently, using gestational age to select the preterm group will likely introduce selection bias in the analysis.

Birth weight can be measured equally in both intervention and control clusters, and it is unrelated to the intervention. Birth weight measurement in the GN clusters is currently being done with high coverage (90%) and good quality. It is likely that some misclassification with small-for-gestational age (SGA) babies will exist, and that this misclassification can underestimate the real benefit of corticosteroids. But it is a conservative approach that will not introduce bias to the comparison between groups.

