GN sites have different mean birth weights; those from Asian sites are much lower than those from African and Latin American sites. Using the same birth weight (e.g., < 2500 g) as a cutoff point at all sites would include a higher proportion of Asian babies, whose mean birth weights are ~2700 g, and most of them would be SGA babies rather than preterm. To avoid this, we will use different cutoff points for each country to select the 10% smallest babies in each GN site. Using data from the MNH study for each GN site, we set a birth weight cutoff point, rounded to 100 g, that would select the smallest 10% of infants as a proxy for preterm births (< 36 weeks GA). Using this rule, the cutoff point for sites in Argentina, Zambia, and Kenya was 2500 g; for sites in Guatemala and Karnataka, India, was 2400 g; and for sites in Nagpur, India, and Pakistan was 2200 g. The overall prevalence of LBW for all sites according to those weight limits is 8.2%, with an 11.4% neonatal mortality at 7 days. A birth weight of 750 g will be used as a cutoff point for the lower birth weight limit for analysis purposes, except for those GN sites where babies with birth weights < 1000 g are considered abortions.

The primary and secondary outcomes in LBW babies, the outcomes in all infants and their mothers, and the process outcomes (to be measured only in the intervention clusters) are shown in Table
1. LBW babies are defined as newborns with birthweight below the 10^th^ percentile of the site.

**Table 1 T1:** Study outcomes

**Outcome measures in infants with birth weight below 10**^**th**^**percentile and their mothers**	**PRIMARY**
	- Neonatal mortality at 28 days

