	**SECONDARY**
	- Rate of antenatal corticosteroid use
	- Maternal infection from birth up to 7 and 42 days postpartum
	- Perinatal mortality rate (stillbirths ≥ 20 weeks GA or ≥ 500 g + neonatal deaths before 7 days)
	- Early neonatal mortality rate at 7 days after birth
	- Mean neonatal weight at 7 and 28 days
	- Neonatal and perinatal mortality rates by country
	- Neonatal and perinatal mortality rates by type of setting (health facility based deliveries vs. community based deliveries)
	- Infant mortality rate at 42 days after birth*.*
**Outcome measures in all infants and their mothers**	- Early neonatal mortality (7 days after birth)
	- Neonatal mortality at 28 days after birth
	- Maternal infection from birth up to 7 days postpartum
	- Maternal infection from birth up to 42 days postpartum
	- Infant mortality rate at 42 days after birth
**Process measures**	- Number of women receiving corticosteroids and number of doses
	- Number of referrals
	- Number of health providers trained
	- Number of kits distributed
	- Health providers’ opinions about the kits
	- Number of kits fully used (all doses administered) at site
	- Number of kits partially used (1–3 doses of dexamethasone) at site

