### Data analysis

The primary analysis will compare post-intervention outcomes between intervention and control clusters, controlling for country, using two complementary approaches. First, a cluster-based permutation test that is appropriate for the stratified randomization process be used to develop a formal hypothesis test and interval estimates of the treatment difference between the two arms. A model-based analysis will be used to assess whether the inferences generated by the permutation test are robust enough to control for potential confounders and to describe any evidence of differential treatment effects in the different countries. Although this study is not powered to evaluate treatment by country interactions formally, any evidence of such interactions will be described through the model-based analysis of this primary outcome.

An intent-to-treat analytic approach will be used for both the permutation test and for the model-based analyses, in that any cluster assigned to the intervention will be considered treated, whether or not the ACT intervention was delivered in that cluster. Also, both analyses will use country as a blocking or stratification variable in the analysis to reflect the randomization scheme.

To facilitate the model-based primary analysis, a detailed analysis of baseline variables of the two groups (intervention and control clusters) will be performed to assess the extent, if any, of baseline imbalances between the two groups of clusters. If baseline differences between the treatment arms are identified, the covariables representing the imbalanced variables will be used for adjusted analyses. Imbalances at the cluster level (e.g., proportion of hospital births, type of birth attendant) can be adjusted in the model-based analysis. Because the primary interest is in the decrease in the marginal neonatal mortality rate at the cluster level, the generalized estimating equations (GEE) method of Liang and Zeger
[21] as implemented through the SAS procedure GENMOD will be used for the primary analysis. The model will control for cluster-level effects by assuming country-specific correlation within clusters, and all inferences will be based on the empirical correlation matrix proposed by Liang and Zeger
[21]. Additional details of the model will be specified in the Statistical Analysis Plan.

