#### *Power estimates*

This trial will be conducted using all of the clusters from the MNH registry determined to have the local infrastructure to implement the protocol. On the basis of preliminary information from the site investigators, we anticipate between 90 and 100 clusters with at least 250 annual deliveries (average of 400) to be available for the trial. Assuming that between 8% and 9% of deliveries are premature, we anticipate a mean cluster size of between 50 and 75 premature newborns for an 18- to 24-month trial. For 28-day neonatal mortality, a study size of 90 clusters with at least 60 LBW deliveries per cluster will have a power of slightly more than 80% (Type I error rate of 0.05) to detect a decrease of 30% in neonatal mortality from 13% to 9%. For the outcome of antenatal corticosteroid use among LBW infants, a sample size of 90 clusters with 50 events per cluster has a power of greater than 0.99 to see an increase in utilization from a start-rate of 10%–20% or more.

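### Birth weight is not pre-specified as a covariate for mean weight at 7 and 28 days, so a possibly useful gain in precision is left to chance

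*Protocol article*

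**What the plan says.** Table 1 of the protocol article lists "Mean neonatal weight at 7 and 28 days" among the secondary outcomes in the low-birth-weight set. Membership of that set depends on birth weight: "LBW babies are defined as newborns with birthweight below the" 10th percentile of their site. The cutoffs are 2500 g in Argentina, Zambia and Kenya and 2400 g in Guatemala and Karnataka, while the cutoff "for sites in Nagpur, India, and Pakistan was 2200 g".

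The section on other secondary outcome measures plans GEE models and generalized linear mixed models. For the GEE models it states that there will be "results reported for both unadjusted analyses and analyses controlling for covariates that differ across clusters"; the mixed models are likewise to be reported unadjusted and adjusted. The Data analysis section uses similar logic for the primary outcome: "If baseline differences between the treatment arms are identified, the covariables representing the imbalanced variables will be used for adjusted analyses". Its examples of such variables are cluster-level ones (share of hospital births, type of attendant). Birth weight is not named as a covariate in either place.

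On birth weight itself, the Outcome measures section says: "Birth weight can be measured equally in both intervention and control clusters, and it is unrelated to the intervention". It adds that its measurement is "currently being done with high coverage (90%) and good quality".

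**The concern.** For a weight measured at 7 or 28 days, birth weight is the natural baseline value. The usual reason to adjust for a baseline value is that it predicts the outcome, which holds whether or not the arms happen to differ on it. A rule that admits covariates only when a difference is observed can leave out the strongest available predictor, and it makes the choice of model depend on the data.

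Precision is what is at stake. The article's secondary objective is safety for women and newborns. A comparison of raw mean weights carries all the spread in birth weight between infants, so a real difference in later weight is harder to see and a null result is less informative. The planned control for country does not replace birth weight. The two Indian sites have different cutoffs (2400 g and 2200 g), so country does not fully absorb the site differences, and no site or country term absorbs the spread between infants within a site.

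**Working it through.** **Inputs from the article.** 90 clusters with 60 small infants each; intracluster correlation (ICC) 0.01 to 0.05, given in the sample-size section and not specific to weight; 1:1 allocation; "Type I error rate of 0.05" (two-sided assumed). No SD, ICC or correlation is given for weight at 7 or 28 days.

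**The article's own power figure.** It concerns mortality (13% against 9%), and none is stated for weight. Infants per arm after the design effect are n = 45 × 60 / (1 + 59 × ICC). At ICC 0.03, n = 2700 / 2.77 = 975. Then z = (0.04 − 1.96 × √(2 × 0.11 × 0.89 / 975)) / √((0.13 × 0.87 + 0.09 × 0.91) / 975) = 0.864, a power of 80.6%. The stated power of slightly more than 80% is therefore reproduced at the middle of the ICC range (96.2% at ICC 0.01, 65.7% at 0.05). This supports using m = 60 and the stated ICC range below, borrowed for weight as an assumption.

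**Variance with and without birth weight.** Let r_w and r_b be the correlations of birth weight with later weight within and between clusters. The ratio of adjusted to unadjusted variance of a cluster mean is

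[ICC × (1 − r_b²) + (1 − ICC) × (1 − r_w²) / m] / [ICC + (1 − ICC) / m].

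*Case A: same correlation within and between clusters.* The ratio reduces to 1 − r².

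| r | variance ratio | fall in variance | SE ratio |
|---|---|---|---|
| 0.5 | 0.75 | 25% | 0.866 |
| 0.7 | 0.51 | 49% | 0.714 |
| 0.8 | 0.36 | 64% | 0.600 |

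More than half of the variance goes only if r exceeds √0.5, about 0.71.

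*Case B: birth weight explains within-cluster variation only (r_b = 0), m = 60.*

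- r_w = 0.8, ICC 0.01: (0.01 + 0.99 × 0.36 / 60) / (0.01 + 0.99 / 60) = 0.01594 / 0.0265 = 0.60, a fall of about 40%.
- r_w = 0.8, ICC 0.05: (0.05 + 0.95 × 0.36 / 60) / (0.05 + 0.95 / 60) = 0.0557 / 0.0658 = 0.85, a fall of about 15%.
- r_w = 0.5: ratios 0.84 and 0.94, falls of about 16% and 6%.

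With m = 50 in place of 60, the r_w = 0.8 ratios are 0.58 and 0.82, so fewer weighed infants per cluster would change little.

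**What correlation is plausible in this set?** Selecting the smallest infants restricts the range of birth weight and lowers the correlation. A simulation assumed birth weight with mean 3000 g and SD 450 g, selection of the lowest 10%, and weight gain independent of birth weight. The birth-weight SD in the selected set was about 186 g. The correlation with later weight was:

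| SD of gain (g) | r | r² |
|---|---|---|
| 100 | 0.88 | 0.78 |
| 150 | 0.78 | 0.60 |
| 200 | 0.68 | 0.46 |
| 300 | 0.53 | 0.28 |

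Gain has had less time to vary by day 7 than by day 28, so the upper rows fit day 7 better and the lower rows day 28.

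**The case against.** There are four serious arguments on the other side.

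*The text does not exclude birth weight.* A reader might infer that weight will be compared with birth weight left out of the model. The article does not say that. An adjusted analysis is planned, and birth weight would enter if it were found to differ. Read literally, the phrase about differences across clusters might even admit it, since mean birth weights differ by site. This stands: the defect is that inclusion is not fixed in advance and, if it happens, its form (individual value or cluster summary) is open.

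*Covariate lists belong in the SAP.* This has some force for a condensed article. But the section on secondary outcomes states its selection rule outright, without the deferral to the SAP that the article makes for the primary model and for missing data. The point is directed at that stated rule.

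*The loss may be modest.* A reader might infer that most of the available precision is thrown away. The article has no figure to support that. It needs a correlation above about 0.71 under the favourable Case A, which is plausible at day 7 and doubtful at day 28. Nor can a large SD be paired with a high correlation: with a birth-weight SD near 186 g, a later-weight SD of 300 to 400 g implies a correlation of about 186/300 = 0.62 to 186/400 = 0.47, not 0.8. Power or interval widths in grams built on such a pairing should not be used. A reader might also fear that a chance birth-weight difference would pass as a growth effect. A visible difference is the case in which the planned rule would trigger adjustment, so that fear is largely met.

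*Birth weight follows an antenatal intervention.* Conditioning on it removes any effect that acts through fetal growth. This is a real limit on interpretation. It is blunted because the article already conditions on birth weight to form the analysis set and asserts that the intervention does not affect it, and because the unadjusted comparison, which keeps such an effect in view, stays in the report.

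**Conclusion.** The point holds in a limited form. For weight at 7 and 28 days, covariates are selected by observed difference, and a prognostic baseline available for every infant in the set is not pre-specified. The consequence is a possible loss of precision on one secondary outcome, not a bias and not an error in the primary analysis.

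Its size cannot be derived from the article. The range shown runs from a 6% fall in variance (r_w = 0.5, within-cluster only, ICC 0.05) to 64% (r = 0.8 at both levels). It depends on the assumed correlation, on whether birth weight explains between-cluster variation, and on an ICC borrowed from the sample-size section. This is a low-cost improvement rather than a necessary correction.

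**What to change.** In the adjusted GEE and mixed models for mean weight at 7 and 28 days, pre-specify the infant's birth weight as a continuous individual-level covariate, together with site, whether or not the arms are seen to differ. Keep the planned unadjusted comparison as a reported result and show mean birth weight by arm beside it. State that the adjusted result is weight given birth weight, and that it relies on the protocol's position that the intervention does not affect birth weight. Leave the primary mortality model as it is.

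The cost is a line or two in the analysis plan. No new data are needed.

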### Sample size

#### *Effect size*

We expect to increase corticosteroids use from less than 10% to at least 50% among preterm births. From the estimates in the systematic review on the effect of corticosteroids on mortality
[4], we expect an associated relative rate reduction in neonatal mortality of 25%–30%. The estimated effect size is lower than the effect observed in the systematic review of clinical trials
[4], to take into consideration that we will use birth weight as a proxy for GA and therefore will include a proportion of term small for GA babies who may not benefit from receiving corticosteroids.

#### *Intracluster Correlation Coefficient (ICC)*

Using the MNH registry baseline data, the ICC is estimated to be between 0.01 and 0.05. The estimate was computed using data from 106 MNH registry clusters.

#### *Power estimates*

This trial will be conducted using all of the clusters from the MNH registry determined to have the local infrastructure to implement the protocol. On the basis of preliminary information from the site investigators, we anticipate between 90 and 100 clusters with at least 250 annual deliveries (average of 400) to be available for the trial. Assuming that between 8% and 9% of deliveries are premature, we anticipate a mean cluster size of between 50 and 75 premature newborns for an 18- to 24-month trial. For 28-day neonatal mortality, a study size of 90 clusters with at least 60 LBW deliveries per cluster will have a power of slightly more than 80% (Type I error rate of 0.05) to detect a decrease of 30% in neonatal mortality from 13% to 9%. For the outcome of antenatal corticosteroid use among LBW infants, a sample size of 90 clusters with 50 events per cluster has a power of greater than 0.99 to see an increase in utilization from a start-rate of 10%–20% or more.

### Ethical aspects

The use of antenatal corticosteroids for women at risk of preterm birth is the standard of care in high-income countries as well as at the hospital level for most of the countries participating in the trial. However, at each participating site, the Institutional Review Board (IRB), Ministry of Health, and physicians will be consulted on guidelines for the use of antenatal corticosteroids to ensure that we are in compliance with cultural, medical, and regulatory policies and norms. These drugs do not require regulatory approval in the participating countries, nor do they require approval from the Food and Drug Administration as an investigational new drug because the research is being conducted outside the United States.

The protocol and the informed consent documents were submitted and approved by the IRBs and ethics committees of all participating clinical sites and Research Triangle Institute (RTI), as the data center.

All participating communities must agree in advance to participate in the study. Community-responsible health authorities will provide their agreement to participate before beginning any activities and will act as cluster ethical guardians. Community education, using forums such as meetings and posters, will inform the community and its authorities about the purpose and procedures of the study. Communities will be informed of their assignment to the control or intervention cluster after randomization.

At the individual level, informed consent to collect data and to administer corticosteroids will be requested. Because high risk for preterm birth is frequently an emergency condition (preterm labor, hemorrhage), to the extent possible, informed consent to administer corticosteroids will be done during pregnancy for all women enrolled in the MNH registry. For those women eligible for corticosteroids administration who were not asked for consent during pregnancy, consent would be sought with identification of the risk of preterm delivery. In this case, women who present at the community or health center level with signs or symptoms that make them eligible to receive corticosteroids, will be consented only if they are in early labor (<6 cm of cervical dilation or the local equivalent), or in a clinical condition not evaluated as an extreme emergency (like severe hemorrhage, or imminent eclampsia).

At the hospital-level, where antenatal corticosteroids are the standard of care for women having high risk of preterm birth, eligible women will not require consent.

All health providers working in the intervention clusters that are eligible to be trained in the intervention procedures will be invited to receive the training and asked for their signed informed consent.
